## **5. STUDY AGENTS**

### **VACCINE**

The BSAM-2/Alhydrogel® vaccine and CPG 7909 will be supplied to the study site pharmacist by the Biopharmaceutical Development Program, SAIC-Frederick, Inc., National Cancer Institute at Frederick, MD, where the materials were formulated and packaged. Each of the 2 components will be supplied separately in single-use vials containing 1 mL of 80 µg/mL BSAM-2/Alhydrogel® (Lot #L0811005), 1 mL of 320 µg/mL BSAM-2/Alhydrogel® (Lot #L0811007), or 0.08 mL of 10 mg/mL CPG 7909 (Lot #L0808002), and labeled for investigational use only.

### **EUVAX B/HEPATITIS B VACCINE**

Euvax B consists of highly purified, non infectious particles of Hepatitis B surface antigen (HBsAg) absorbed onto aluminum salts as an adjuvant and preserved with thimerosal. It is a recombinant DNA hepatitis B vaccine derived from HBsAg produced by DNA recombinant technology in yeast cells (*Saccharomyces cerevisiae*). Other excipients are potassium phosphate monobasic, sodium phosphate dibasic and sodium chloride. Euvax B is for intramuscular use only. The vaccine is manufactured by LG Life Sciences, based in the Republic of Korea. The vaccine meets the WHO requirements for recombinant hepatitis B vaccines, and is widely used and available in Mali. No substances of human origin are used in its manufacture. While the recommended vaccination schedule is for 0, 1, and 6 months, per the Centers for Disease Control, recombinant hepatitis B vaccines may be administered on a 0, 1, and 4 or 0, 2, and 4 month schedule with dose-specific and final rates of seroprotection similar to those obtained on a

0, 1, and 6 month schedule. (MMWR Recommendations and Reports, December 8, 2006 / 55(RR16);1-25).

### **VACCINE ADMINISTRATION**

The trial site pharmacy will prepare the point-of-injection formulation. Shortly before vaccination, 0.7 mL of BSAM-2/Alhydrogel® is withdrawn and added to the single dose vial containing 0.08 mL CPG 7909. The vial is then mixed. This formulation is referred to as BSAM-2/Alhydrogel®+CPG 7909. The vaccine must be administered not more than 6 hours after mixing the BSAM-2/Alhydrogel® with the CPG 7909 and should be stored at 2-8°C if not immediately administered. When ready to administer BSAM-2/Alhydrogel®+CPG 7909, 0.55 mL is withdrawn into a syringe and the vaccine is injected. A 0.55 mL dose of the vaccine corresponds to 500 µg of CPG 7909 and either 40 µg (low dose) or 160 µg (high dose) of BSAM-2, depending on the dose of BSAM-2/Alhydrogel®. (The actual dose of CPG 7909 will be 564 µg but is shown here and elsewhere as 500 µg for simplicity. The actual antigen dose in 0.55 mL is 39.5 µg (low dose) and 158.0 µg (high dose).)

### **VACCINE STORAGE**

BSAM-2/Alhydrogel® vaccine, CPG 7909, and Euvax B/Hepatitis B vaccine will be transported and stored at temperature-controlled conditions, as per SOP. Temperature data loggers will accompany the vaccines at all times to ensure storage temperature limits have not been violated. Vaccines and adjuvant should NOT be frozen at any time. Refrigerator temperature will be continuously monitored.

### **VACCINE ACCOUNTABILITY**

#### **5.1.1 Disposition**

After administration of a vaccine dose, the single-dose vial will be returned to the Pharmacy at the test site, and vials will be accounted for and stored until monitoring by the IND Sponsor. The used vials may then be disposed of according to site standard operating procedures after monitoring has been completed.

#### **5.1.2 Documentation**

The trial site pharmacist is responsible for maintaining an accurate inventory and accountability record of vaccine supplies for this study. Partially used vials may not be administered to other subjects.

## **6. STUDY PROCEDURES**

### **SCREENING**

The purpose of the screening visit is to determine volunteer eligibility for study participation. Subjects in the US who are diagnosed with a medical condition during the screening process (e.g., test positive for hepatitis B, hepatitis C, or HIV) will be notified and referred for medical care. In Mali, any clinically relevant finding that is discovered upon screening will be treated appropriately according to the standard of care as follows: initial management will be performed at the study clinic, free of charge. Should referral for more extensive investigation or treatment be required, the study will arrange and pay for transportation to a National Hospital and initial

consultation. Initial care according to the standard of care in Mali will be covered by the study; however, in the event that a chronic illness is discovered during the course of screening, long-term treatment and care will not be reimbursed by the study.

The following screening evaluation for this study must be completed within the 60 days prior to vaccination.

- Explain the study and Informed Consent to the subject
- Ensure the subject has signed the Informed Consent and receives a signed copy of the Informed Consent, and has correctly answered all questions on the Informed Consent Comprehensive Exam
- Explain the HIV Informed Consent and obtain a signed copy from the subject (US only)
- Elicit a complete medical history, including menstrual and contraceptive history and/or history of surgical sterility for females
- Administer a complete physical examination
- Obtain a signed medical release of information form from the patient (US only)

Obtain approximately 25 mL of blood for complete blood count (CBC) with differential and platelet count, ALT, creatinine, anti-dsDNA, hepatitis B surface antigen, hepatitis C antibody, HIV antibody (US only) and malaria smear and filter paper blood collection (Mali only) in all subjects. Obtain urine for pregnancy testing and dipstick testing for protein and blood.

#### **ASSIGNMENT TO GROUPS**

Subjects in the US will be assigned to dose groups in the order in which they are successfully screened. The Mali phase of the trial will be randomized and subjects will be blinded. Clinical investigators and other personnel in Mali conducting screening will also be blinded to the randomization code.

#### **BLINDING AND RANDOMIZATION (MALI)**

Vaccinations in Mali will be single-blinded, with half of the subjects receiving the comparator vaccine, Euvax B/ Hepatitis B Vaccine. The comparison group will allow for better interpretation of antibody levels in a population which has pre-existing antibody titers to the vaccine antigens, and which may experience malaria infection during the vaccination period, which would also affect antibody titers. Blinding will also allow for more objective assessment of adverse events in this population, which has a higher rate of febrile illness and other clinical events which could be perceived as related to vaccination. The study pharmacist will be aware of the vaccination assignment (BSAM-2/Alhydrogel®+CPG 7909 versus Euvax B/ Hepatitis B Vaccine), but subjects and clinical investigators responsible for assessment of adverse events will not be aware of vaccination assignment until the completion of the study. Syringes will be covered by a sleeve or opaque tape to mask their appearance and preserve blinding. In addition, vaccines will be administered by investigators who are not involved in assessment of adverse events. The senior investigators in Mali may choose to remain blinded, but will have access to the study codes if necessary. Randomization codes and labels will be generated by the study statistician, and will be used by the study pharmacist as per SOP. The study numbers will be assigned in the order in which participants are vaccinated.

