## **ASSESSMENT OF ADVERSE EVENTS**

### **9.1.1 Identification of Adverse Events**

Assessment of safety will include clinical observation and monitoring of hematological, chemical, and immunologic parameters. Safety will be evaluated by monitoring of subjects for local and systemic adverse reactions during the course of the trial. Subjects will be closely monitored for 30 minutes following each immunization. Additionally, subjects will return to the

clinic on Days 1, (Mali only) 2, (Mali only) 3, 7, and 14 following each vaccination for clinical assessments, and approximately monthly thereafter until completion.

All AEs will be graded for severity and assessed for relationship to the study product. Reactions will be graded as described in **Section 9.1.2** in this protocol. A study clinician will be available 24 hours a day during the study evaluation period; a study clinician will stay in Bancoumana for the duration of the trial and will be available to the study participants at all times. Should a subject call on a study clinician to report an adverse event, it will be fully documented in the subject's study chart, and discussed with the Principal Investigator.

All local and systemic reactions will be captured on the appropriate case report form (CRF). Those assessed as serious will be further reported on the Sponsor's SAE report form. Adverse events judged to be possibly, probably, or definitely related to the study product will be followed to adequate resolution.

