#### 9.1.2 Determination of Severity

Severity of AEs will be assessed by the investigator as described in **Appendixes C, D, and E**. AEs not included in the Appendixes will be graded for severity using the followings definitions:

|                             |                                                                                                                                                                  |
|-----------------------------|------------------------------------------------------------------------------------------------------------------------------------------------------------------|
| Grade 1 (Mild):             | No effect on activities of daily living                                                                                                                          |
| Grade 2 (Moderate):         | Partial limitation in activities of daily living (can complete $\geq 50\%$ of baseline), or treatment given; no or minimal medical intervention/therapy required |
| Grade 3 (Severe):           | Activities of daily living limited to $< 50\%$ of baseline, medical evaluation/therapy required                                                                  |
| Grade 4 (Life-threatening): | Extreme limitation in activity, significant assistance required; immediate medical intervention or therapy required to prevent death                             |
| Grade 5:                    | Death                                                                                                                                                            |

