## **HALTING RULES**

The Principal Investigator will closely monitor study data as they become available and will make determinations regarding the presence and grading of adverse events. Adverse events will be evaluated with regard to the known complications associated with administration of CPG 7909 and other vaccine components. If a dose of vaccine is considered unacceptably reactogenic (as described in the following criteria), the study will be halted. No new enrollments and no further vaccinations will be administered by the Investigators until reviewed by the SMC and study IND Sponsor. A report of SMC recommendations will be submitted to the IRB. The following criteria will be used to define unacceptable reactogenicity of the malaria vaccine:

1. One or more subjects experience an SAE as defined in **Section 9.2** of this protocol that is determined to be possibly, probably, or definitely related to the vaccine, **or**
2. One or more subjects experience a hypersensitivity reaction that is probably or definitely related to the vaccine, **or**
3. Any severe clinical illness occurs that is not explained by a diagnosis that is unrelated to vaccination, **or**
4. Two or more subjects in any dose cohort (low dose US, high dose US, or Mali) experience any Grade 2 or higher laboratory abnormality (see **Appendix D**), or Grade 3 systemic AE that is determined to be possibly, probably, or definitely related to the vaccine as defined in this protocol. This does not include Grade 2 neutropenia resolving within 7 days of vaccination, which is an expected laboratory abnormality with CPG 7909 and which has not been associated with clinically significant events.

The IRBs, the NIAID, the pharmaceutical supporter(s), the FDA, or other government agencies, may discontinue the study at any time. Subsequent review of serious, unexpected, and related adverse events by the Medical Monitor, SMC or IRB, the IND sponsor, the FDA, and other regulatory authorities may also result in suspension of further administration of vaccine at the clinical site. The FDA, other regulatory authorities, and the study sponsor(s) retain the authority to suspend additional enrollment and administration of vaccine for the entire study as applicable.

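### The Mali blinding rules do not stop an investigator with code access, possibly the Principal Investigator, from judging adverse events

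*Protocol*

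**What the plan says.** - **The promise.** Protocol, Blinding and Randomization (Mali): "subjects and clinical investigators responsible for assessment of adverse events will not be aware of vaccination assignment until the completion of the study". One reason given for blinding is a more objective judgement of adverse events, because febrile illness is common in this population and could be put down to the vaccine.
- **The exception.** The same section: "The senior investigators in Mali may choose to remain blinded, but will have access to the study codes if necessary". It does not say who counts as a senior investigator, what makes access necessary, who approves or records it, or whether it is limited to single subjects.
- **Who decides.** Halting Rules section: "The Principal Investigator will closely monitor study data as they become available and will make determinations regarding the presence and grading of adverse events". There is no blinding condition and no carve-out for Mali, although rule 4 of that section names Mali as a cohort. Section 9.1.2 says "Severity of AEs will be assessed by the investigator" without saying which investigator. Section 9.1.3 names nobody for relatedness. Under Section 9.1.1, when a subject calls a study clinician about an event, "it will be fully documented in the subject's study chart, and discussed with the Principal Investigator".
- **The one separation that is written.** Those who give the vaccine are kept out of adverse-event assessment. Nothing equivalent is written for senior investigators or the Principal Investigator.
- **Where the judgements go.** The primary endpoint is the incidence and severity of adverse events. Section 11.1.1 compares the proportion with at least one event between vaccine groups within site, and summarises events by severity and relationship.

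**The concern.** Mali is the only part of the trial with a comparator, so it is the only place where blinding can protect a vaccine-versus-control contrast in adverse events. The protocol saw the risk and closed it for the vaccinators, but left it open for people who may sit above the day-to-day assessors. If someone who has seen the codes settles whether an event is present, how it is graded or whether it is related, those judgements can drift by arm. The safety estimates and the halting decisions both depend on them.

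**Working it through.** The point rests on the text, so the main check sets the provisions side by side.

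| Role in Mali | Knowledge of assignment | Part in adverse-event judgement |
|---|---|---|
| Subjects | Blinded to study completion | Report symptoms |
| Investigators assessing events | Blinded to study completion | Assess events |
| Pharmacist | Knows | None stated |
| Vaccinators | Not stated; syringes masked | Expressly none |
| Senior investigators | Blinding optional; code access if needed | Not stated, not barred |
| Principal Investigator | Not stated | Determines presence and grade; consulted on events that subjects call in |

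**Step 1: does one person fall under two rules?** The last two rows conflict with the second only if the Mali Principal Investigator is a senior investigator. The protocol does not say so. It is the natural reading, and nothing excludes it. The Benefits section also has a senior physician-investigator monitor the medical management of participants hospitalised in Bamako. That brings a senior investigator close to serious events, without making that person the assessor.

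**Step 2: which judgements leave room for discretion?** Appendix C grades fever, erythema, swelling and induration on numeric limits, and Appendix D does the same for most laboratory tests. Section 9.1.3 fixes relatedness by rule for local reactions (related) and clinical malaria (not related). What remains is:
- whether an event is present;
- the grade of symptoms scored by their effect on daily activity (injection-site pain, headache, nausea, malaise, myalgia, arthralgia);
- the relatedness of non-local events.

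**Step 3: what do these feed?** Presence and grade make up the primary endpoint. Relatedness enters halting rules 1, 2 and 4, and the grade of systemic events also enters rule 4.

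**Step 4: size.** Thirty Mali participants randomized 1:1 give 15 per arm. One subject is 1/15 = 6.7 percentage points of an arm's proportion. Rule 4 is met by two subjects in a cohort. As an illustration only: the protocol's account of US experience reports Grade 3 systemic events in 4 of 30 volunteers (malaise in two, fever and headache in the other two). If that rate carried over to Mali, which is an assumption, 15 vaccine recipients would yield 15 × 4/30 = 2.0 on average, right at the rule 4 threshold.

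**Step 5: the plan's own figure.** The sample-size statement gives a probability of 0.80 of seeing at least one event with n = 12 and p = 0.125. This reproduces: 1 − 0.875^12 = 0.799 (0.865 at n = 15). Blinding does not enter it, so the figure neither supports nor weakens the point.

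**The case against.** The section can be read consistently. The rule that assessors stay blinded is categorical; pharmacist, vaccinators and senior investigators are then treated as separate roles. On that reading a senior investigator who uses the codes is simply not an assessor. The Halting Rules sentence is written once for the whole trial, open-label US part included, and the protocol lists three Principal Investigators, so it need not override a Mali-specific rule. Discussing an event with the Principal Investigator is not grading it. Mali is labelled single-blinded, access is limited to need, and an independent medical monitor and the Safety Monitoring Committee stand behind the investigators.

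Much of this stands. The link between senior investigators and the Principal Investigator is inference, and the day-to-day assessors are described as blinded. But the consistent reading needs a sentence that the protocol lacks: one keeping code-holders out of adverse-event determinations, as is done for vaccinators. The single-blind label does not settle it, because the same section extends blinding to assessors. Outside review also does not restore blinding at the first judgement.

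A reader might also infer that one regraded subject would overturn the between-arm test. At invented counts, Fisher's exact two-sided p is 0.042 for 5/15 v 0/15 and 0.0996 for 4/15 v 0/15. The arithmetic is right, but the inference fails. The planned comparison uses the proportion with at least one adverse event, and regrading leaves that unchanged; only a decision on whether an event occurred can alter it, and only in a subject with no other event. An arm with no events at all is implausible after three injections with active follow-up. Section 11.1 calls the study exploratory, so crossing 0.05 decides nothing.

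**Conclusion.** The provisions need to be reconciled. As written, and provided that the Mali Principal Investigator is among the senior investigators, the protocol permits unblinded judgement of event presence, of the grade of subjective symptoms, and of the relatedness of non-local events. A reader might infer that the Mali primary endpoint will be judged unblinded. The documents do not support that: they show permission, not practice, and they do not state the Principal Investigator's blinding status either way. The size is modest but not negligible: 6.7 percentage points per subject in an arm of 15, and a halting threshold of two subjects. The point does not touch the US part, which is open label, or events graded on numeric limits. It merits correction because it bears on the primary endpoint and on halting in the only controlled part of the trial, and is cheap to remove.

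**What to change.** Amend two places so that they agree.

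1. **Blinding and Randomization (Mali).** Remove the option for senior investigators to decide whether to stay blinded. Say that codes are opened for single subjects only, when needed, with the person, reason and date recorded. Anyone who accesses a code takes no further part in determining presence, grade or relationship of adverse events for the subjects concerned. Define senior investigator, or drop the term.
2. **Halting Rules (Section 9.5), with Sections 9.1.1 to 9.1.3.** State that in Mali everyone who determines presence, grade or relationship, the Principal Investigator included, stays blinded until study completion.

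The cost is protocol and procedure wording. The pharmacist already knows the assignments and the statistician generates the codes, so no new code-holder is needed. The drawback is one extra step when a code is wanted urgently. A sensitivity analysis leaving out assessments made after an unblinding is optional and can be left to the analysis plan.

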## **IMMUNIZATION PROCEDURE**

The study schedule and approximate amounts of blood drawn are summarized in **Appendix B**.

## **CLINICAL MONITORING AND EVALUATION**

Note: Vaccinations will be given on a 0, 2, and 6 month schedule in the US, and a 0, 2, and 4 month schedule in Mali, to allow for the third vaccination to occur just prior to the malaria transmission season in Mali.

### **Study Day 0 (Day of First Vaccination)**

1. Verify that Informed Consent was obtained.
2. Verify that all applicable eligibility criteria have been met.
3. Ensure that CBC, ALT, and creatinine measurements from screening tests are within protocol-defined limits (**Section 4.5** Exclusion Criteria) before vaccinating.
4. Perform abbreviated history and physical examination, focusing on any acute complaints.
5. Mali only: during the physical examination, study staff will educate the subject regarding signs and symptoms of potential adverse events (AEs), and indications for use of antipyretics (acetaminophen/paracetamol, or ibuprofen) if fever, headache, or malaise occurs.
6. Obtain approximately 55 mL of blood for CBC with differential and platelet count, ALT, creatinine, anti-AMA1 and anti-MSP1 antibody ELISA, parasite growth inhibition assay (GIA), and B and T cell studies. An additional 5 mL of blood will also be obtained and serum will be stored. If subsequent to second vaccination the subject develops clinical signs of autoimmune or other disease, this sample will be used for baseline laboratory tests as indicated. The total volume of blood to be drawn is 60 mL.
7. Obtain blood for malaria smear, filter paper collection and urine for chloroquine testing (Mali only).
8. Obtain a urine sample for dipstick testing and ensure that protein and blood are no more than trace positive before vaccinating. Should a female subject have more than trace blood in her urine on Day 0, she will not be excluded from vaccination if she is currently menstruating.
9. For females, obtain a urine or serum sample for  $\beta$ -hCG testing. Ensure that the test is negative before vaccinating; a positive test will exclude the subject from the trial.
10. Record vital signs (blood pressure, temperature, heart rate, and respiratory rate).
11. Administer the vaccine.
12. Observe for at least 30 minutes after vaccination to evaluate for immediate adverse reactions.
13. US only: education by study staff during 30-minute post-immunization wait period describing proper use of digital thermometer, injection-site reaction measurement, and malaria vaccine side-effect memory enhancement tool. Study staff will also discuss signs and symptoms of potential AEs, and indications for use of antipyretics (acetaminophen/paracetamol, or ibuprofen) if fever, headache, or malaise occurs.

